### Statistical analysis

The intent-to-treat population will be used for the primary efficacy analysis and includes all patients who had any exposure to ferumoxytol or iron sucrose during the postrandomization period of the study. The evaluable population for the main study includes all patients who meet all inclusion criteria and do not violate any exclusion criteria, receive 2 doses of ferumoxytol (1.02 g) or all 10 doses of iron sucrose at the initial treatment period, and have evaluable data for hemoglobin (primary endpoint) at the treatment period Baseline and Week 5. For the “oxidative stress” substudy, the evaluable population includes all patients who receive 2 doses of ferumoxytol (1.02 g) or all 10 doses of iron sucrose at the initial treatment period and have at least one of the evaluable blood biomarkers of oxidative stress/inflammation at the treatment period Baseline and Week 5. For the MRI substudy, the evaluable population includes all patients who receive study drug and have at least one pair of evaluable Baseline and post-Baseline image data on any of the defined MRI endpoints. The safety population includes all patients who have any exposure to study drug during the study.

A sample size of 240 patients provides approximately 90% power for testing noninferiority of ferumoxytol to iron sucrose, assuming a noninferiority margin of 0.5 g/dL (5.0 g/L), a one-sided alpha of 0.025, and a standard deviation of 1.13 g/dL (11.3 g/L) for the primary endpoint. The noninferiority margin of 0.5 g/dL (5.0 g/L) was selected because it represents 50% of the minimum clinically meaningful change in hemoglobin 1.0 g/dL (10.0 g/L; the expected clinical response with transfusion of 1 unit of packed red blood cells).

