#### Biomarkers

Blood samples for determination of biomarkers assessed in the “oxidative stress” substudy will be collected for patients randomized to ferumoxytol before and after each of the 2 doses and at Week 5 in the initial treatment period. For those in the iron sucrose group, samples will be collected before and after the 1st, 2nd, and 10th doses and at Week 5 during the initial treatment period. Biomarkers to be assessed include protein carbonyl content, 13-hydroxyoctadecadienoic acid, 4-hydroxynonenal, monocyte chemoattractant protein-1, neutrophil gelatinase-associated lipocalin, and high-sensitivity interleukin-6. Assays of biomarkers will be conducted at a central laboratory.

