### Study endpoints

Endpoints for the main study are shown in Table 3. The primary efficacy endpoint is the mean change in hemoglobin from Baseline to Week 5 for each treatment period. The primary safety evaluation is the assessment of the AE profile over the course of the study. The substudies examine exploratory endpoints. The “oxidative stress” substudy (exploratory safety endpoint) will assess the mean change in biomarkers of oxidative stress/inflammation from Baseline to Week 5 of the initial treatment period in the main study. For the MRI substudy (exploratory endpoint), the primary endpoint is the absolute change in cardiac MRI T2* from Baseline to each follow-up evaluation (i.e., at approximately 6, 12, and 24 months after initial dosing [main study treatment period day 1]) as well as the percentage of an abnormal cardiac T2* occurrence, which is defined as a value of <20 msec. Some secondary endpoints include the proportion of patients developing abnormal cardiac iron deposition (defined as T2* value <20 msec) at any time point, proportion of patients developing cardiac T2* value <10 msec at any time point, change in liver iron concentration, and pancreatic T2*. Measurement of T2* has become the noninvasive standard for evaluation of iron overload and is the most sensitive to iron deposition [19, 20]. Other secondary endpoints for the MRI substudy are summarized in Table 4.

**Table 3 Tab3:** Ferumoxytol for Anemia of CKD Trial endpoints and safety evaluations: main study and oxidative stress substudy

Endpoints	
Main study	
Primary efficacy endpoint	•Mean change in hemoglobin from Baseline to Week 5 for each treatment period
Secondary efficacy endpoints	•Mean change in transferrin saturation from Baseline to Week 5 for each treatment period •Proportion of patients with an increase in hemoglobin of ≥1.0 g/dL at any time from Baseline to Week 5 for each treatment period
Safety evaluations	•An evaluation of the AE profile over the course of the study and following each course of ferumoxytol or iron sucrose, including serious AEs, AEs leading to study drug discontinuation, all AEs, vital signs (blood pressure, heart rate, respiration rate, and body temperature); physical examination findings; and routine laboratory parameters (hematology, chemistry, and iron panel)

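### The only population defined for the oxidative stress substudy requires the full initial course, so non-completers fall outside it even with Baseline and Week 5 biomarkers

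*Protocol article*

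**What the plan says.** All of this is in the protocol article.

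- **Biomarker set (Statistical analysis).** The dosing rule reads "the evaluable population includes all patients who receive 2 doses of ferumoxytol (1.02 g) or all 10 doses of iron sucrose", counted over the first course. A second rule, on data, asks that these patients "have at least one of the evaluable blood biomarkers of oxidative stress/inflammation at the treatment period Baseline and Week 5". Both conditions must be met.
- **Status of the endpoint (Study endpoints).** The text describes the "substudy (exploratory safety endpoint) will assess the mean change in biomarkers of oxidative stress/inflammation from Baseline to Week 5", within the first course only. Table 3 lists the six biomarkers under exploratory endpoints.
- **MRI substudy set (Statistical analysis).** Here "the evaluable population includes all patients who receive study drug and have at least one pair of evaluable Baseline and post-Baseline image data". No full-course condition applies.
- **Other sets (Statistical analysis).** "The safety population includes all patients who have any exposure to study drug during the study". "The intent-to-treat population will be used for the primary efficacy analysis"; it too rests on any exposure. No other analysis is tied to a population by name.
- **Sampling (Biomarkers).** In the comparator arm, "samples will be collected before and after the 1st, 2nd, and 10th doses and at Week 5". In the ferumoxytol group samples are taken around both doses and at Week 5.

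**The concern.** Completing the course happens after randomization and depends partly on how treatment is tolerated. Making it a condition of membership means that the two arms compared are no longer the randomized ones but those who got through their course. For a question about harm this is awkward, because a patient whose dosing was stopped for a reaction cannot enter the set, whatever samples are available.

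The condition is also unequal by construction. One arm must receive 2 doses and the other 10 over about 3 weeks (Randomization and interventions), so there are more occasions to miss or stop in the iron sucrose arm. The trial is open-label, and the Discussion accepts that investigators could not be blinded, so a decision to stop can be influenced by knowing the drug.

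At stake is the direct comparison of the two drugs on oxidative stress that the Discussion says the substudies will deliver. The main efficacy result and the adverse event results are not affected.

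**Working it through.** **Plan's own figure.** The article gives no sample-size or power figure for this substudy, so there is none to reproduce on this point. Its one such figure, about 90% power for 240 patients in the main study, does reproduce. With 160 and 80 patients, SE = 1.13 × √(1/160 + 1/80) = 0.155 g/dL, 0.5/0.155 = 3.23, 3.23 − 1.96 = 1.27, and power is 0.898. Nothing below depends on it.

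**Step 1: who is excluded.** Take a substudy patient who stops before the last dose but gives samples at Baseline and Week 5.

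| Set | Condition on dosing | Patient included? |
|---|---|---|
| Oxidative stress evaluable | full initial course | no |
| MRI evaluable (same rule applied to image data) | any study drug | yes |
| Safety | any exposure | yes |

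The stated endpoint, change from Baseline to Week 5, can be computed for this patient, so it is the dosing condition alone that excludes. The article does not say how many non-completers would attend Week 5, and the point concerns only those who do.

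**Step 2: how unequal exclusion could be.** The article gives no stopping rate. Assume, for illustration, the same chance h of stopping after each dose but the last. Ferumoxytol then has 1 chance to stop and iron sucrose has 9, so the excluded shares are h and 1 − (1 − h)^9. The Oxidative stress substudy section gives about 50 patients per group.

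| h | Ferumoxytol excluded | Iron sucrose excluded | Of 50 per group |
|---|---|---|---|
| 0.5% | 0.5% | 4.4% | 0.25 against 2.2 |
| 1% | 1.0% | 8.6% | 0.5 against 4.3 |
| 2% | 2.0% | 16.6% | 1.0 against 8.3 |

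**Step 3: what that does to a mean.** If a share e of an arm is excluded and those patients differ from completers by d (in SD units of the biomarker change), the completers' mean differs from the full-arm mean by e × d. With d = 0.5 assumed:

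- e = 5%: 0.05 × 0.5 = 0.025 SD
- e = 15%: 0.15 × 0.5 = 0.075 SD

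Applied to the three rows of Step 2, with the same d in both arms, the shift in the arm difference is 0.5 × (0.044 − 0.005) = 0.020 SD, 0.5 × (0.086 − 0.010) = 0.038 SD and 0.5 × (0.166 − 0.020) = 0.073 SD.

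**Step 4: against the precision.** With 50 per group the standard error of the arm difference is √(1/50 + 1/50) = 0.20 SD. If the main study's 2:1 ratio carried over to the substudy as 67:33, it would be √(1/67 + 1/33) = 0.21 SD, so the split hardly matters. The Step 3 single-arm shifts are 0.025/0.20 = 0.125 to 0.075/0.20 = 0.375 of a standard error. To reach one full standard error in one arm, e × d must equal 0.20, for example 10% excluded with d = 2 SD.

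**The case against.** **The article defines this set but does not say that the biomarkers are analysed only in it.** This stands. The main study has an evaluable population with the same dosing condition, and there the primary analysis uses intent-to-treat. The substudy set could likewise be a per-protocol type of set beside an all-exposed analysis, and the full protocol or SAP, which are not shown, may specify one. A reader might infer that completers are the only patients analysed, but the article does not go that far. What it does fix is the definition, and it offers no other set specific to this substudy.

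**Patients stopped for a reaction are not lost to the safety assessment.** This also stands. The Safety assessments section covers adverse events leading to discontinuation, acute hypotension and hypersensitivity, and the safety population needs only exposure. What can be lost is their value in an exploratory biomarker endpoint.

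**The direction of bias is unknown.** A reader might infer that selecting those who tolerate treatment hides induced inflammation. The documents do not support that. The endpoint is at Week 5, the rule removes non-completers for every reason, and a patient who stopped early has received less iron. Including such patients could dilute an effect as easily as reveal one.

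**The MRI set is an imperfect model.** This stands in part. The MRI substudy follows patients for two years with retreatment as needed, so a fixed course is less natural there. Still, the article gives no reason for the stricter rule in the biomarker substudy.

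**Conclusion.** The point holds as a flaw in a stated definition. The only population specific to the oxidative stress substudy selects on course completion, a condition that is harder to meet with 10 doses than with 2, in an open-label trial and for an endpoint that the article itself labels as safety. Non-completers with usable Baseline and Week 5 values are left out of it.

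Neither the size nor the direction of any bias can be determined from the documents, which give no stopping rate and no biomarker variability. Under the assumed 0.5 SD difference and 5-15% exclusion, the shift in an arm mean is well under half a standard error. A material distortion would need frequent stopping or very different non-completers, such as an excess of 2 SD or more in a tenth of an arm, and nothing in the documents supports assuming that. The endpoint is exploratory, so this is a change worth making because it is nearly free and keeps the comparison close to the randomized one. It does not threaten the trial's main conclusions.

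**What to change.** In the Statistical analysis section, define the main oxidative stress analysis set as all substudy patients who receive any study drug and have both a Baseline and a Week 5 value of the biomarker being analysed, grouped as randomized. The second value has to be the Week 5 one: any earlier post-dose sample would admit patients for whom the stated endpoint cannot be computed. Keep the full-course set as a sensitivity analysis, and state that the first set is the main one.

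The cost is a wording change and one repeated table, with no new samples or visits. The downside is that a few partly dosed patients enter the main analysis, which may slightly dilute a full-course effect. The sensitivity analysis shows by how much the two results differ.

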## Discussion

FACT will be the longest randomized controlled clinical trial comparing 2 IV iron products in patients with CKD and IDA on hemodialysis. The study will provide efficacy and safety data from a long-term head-to-head trial of IV iron therapy in hemodialysis patients with CKD and IDA, and these results may provide valuable information that addresses knowledge gaps on the use of IV iron in these patients [9]. The study will also address some recognized concerns regarding IV iron therapy, particularly with respect to the impact of IV iron on oxidative stress/inflammation and the longer-term potential for iron overload.

In particular, the FACT study will provide a direct comparison of the efficacy of ferumoxytol versus the recommended dose of IV iron sucrose [21] over 13 months, providing comparative effects of these agents on hematology and iron panel parameters. One limitation of the study was the inability to blind the investigators to study drug due to the different dosing regimens of each drug. However, the primary and secondary efficacy and safety assessments were conducted outside the timeframe for treatment administration, thus limiting the potential for bias. The study will also provide a long-term assessment of the comparative safety of these 2 agents. Furthermore, the substudies will provide a direct comparison of the effect of ferumoxytol and iron sucrose on oxidative stress and the potential for the long-term use of these agents to result in iron deposition in tissue over 2 years. Preclinical data suggest that some IV iron preparations (e.g., iron sucrose and ferric gluconate) induce oxidative stress, whereas ferumoxytol was bioneutral in this regard [22, 23]. Thus, there may be differences in the pro-oxidant effects among IV iron formulations that may be determined by the assessment of oxidative stress associated with various formulations. The study will also provide useful insights into the use of MRI T2* for monitoring iron overload in patients receiving long-term iron supplementation. Thus, FACT fulfills the need for long-term comparative head-to-head studies of IV iron in hemodialysis patients with CKD and IDA, providing an opportunity to assess multiple aspects of safety and efficacy with ferumoxytol in the longest evaluation of 2 IV iron products to date. Recruitment to the study has ended, and completion of the main study is expected soon.

## Abbreviations

AE: Adverse event
CAPD: Continuous ambulatory peritoneal dialysis
CKD: Chronic kidney disease
ESA: Erythropoiesis-stimulating agent
Hb: Hemoglobin
HD: Hemodialysis
ICF: Informed consent form
IDA: Iron deficiency anemia
IV: Intravenous
MRI T2*: T2-weighted magnetic resonance imaging
NDD: Non-dialysis dependent
PD: Peritoneal dialysis
PI: Prescribing information
rHuEPO: Recombinant human erythropoietin
TP: Treatment period
TSAT: Transferrin saturation
